## Abstract

**Background:**

Vulvar lichen sclerosus (VLS) is a lymphocyte-mediated disease of unknown etiology that can cause intense itching as well stenosis, hindering the evacuation and urination. It can also limit the sex life due to severe local pruritus, pain and dyspareunia (pain during sexual intercourse). The standard treatment for this disease is the use of topical corticosteroids to reduce the clinical symptoms and to try to increase disease-free intervals. Photodynamic therapy (PDT), a treatment that associates a light radiation with a photosensitizing agent and photobiomodulation (PBM) are therapies that can promote effective immunomodulatory responses at the application site by means of photophysical and photochemical phenomena from the molecular to the systemic level, which promote their use in chronic dermatoses. The aim is to compare the effects of PDT, PBM, and topical corticosteroid in VLS evaluating clinical, histological, immunohistochemical and spectroscopic responses.

**Methods:**

The study is prospective, randomized and controlled, in a population of 60 women with histological diagnoses of VLS. There will be 3 treatments groups: PDT, PBM and topical corticosteroid (control group), where will be allocated by randomization 20 patients in each one. The clinical course will be monitored by measuring local temperature, itching, atrophy, and the area of the lesion. Histologically, the slides will be classified and will have the ordering of collagen fibers quantified. Immunohistochemical analysis will be done using the markers IFN-γ, TGF-β, CD4, CD8, IL-1, p53 and Ki-67. Finally, the spectroscopic evaluation will be done by reflectance. Descriptive and inferential statistical analyses will be conducted to compare the groups and make associations between different responses. The study is an open-label for patients with active symptomatic disease with a period of 1 year follow-up to determine the rate of recurrence in each groups.

**Discussion:**

The immunological effects of PDT and PBM are described by several authors in inflammatory skin diseases, stimulating the production and organization of the associated collagen. Thus, it is reasonable to determine the efficacy and safety of these new treatments in VLS, in comparison to the control group, analyzing the recurrence time, the impact on the optical properties of the skin, and the benefit to patients.

**Trial Registration:**

ClinicalTrials.gov: NCT02416531.

## Background

The pathogenesis of vulvar lichen sclerosus (VLS) is idiopathic, but some theories are described, such as the genetic theory, in which it is believed that about 22% of the lichen can be inherited [1]. There is the theory of hormonal changes due to decreased levels of dihydrotestosterone and androstenedione, and reduced activity of the enzyme 5 α reductase [2]. Autoimmune factors and oxidative stress have also been accepted due to the high association with autoimmune disease and the presence of highly specific antibodies against the extracellular matrix protein (ECM 1) [3]. Researchers have reported an autoimmune phenotype characterized by increased levels of Th1-specific cytokines, dense infiltration of T cells, and increased BIC/miR-155 expression [4]. Even though recent work has shown for the first time that vulvar lichen sclerosus is associated with 5-hydroxymethylation and altered expression of IDH enzymes, providing evidence for an epigenetic factor in the pathogenesis, literature is still reticent to establish it as an autoimmune disease [5]. Finally, there is the infectious theory of local factors, whose trauma and friction have been described, but as yet without evidence [6].

Vulvar lichen sclerosus affects the genital skin causing intense itching, whitening and atrophy, and this can cause stenosis, resulting in vulvodynia, pain on urination and bowel movements [7, 8]. It is the second leading cause of non-neoplastic vulvar disease, and is considered the most common cause of chronic vulvar disease with an estimated prevalence of 1:30–1:1000 [9]. The genital form is 5 to 10 times more frequent in women over 40 years and affected females outnumber males by 10:1 [10]. Anogenital involvement is 85% and extragenital is 15% [11]. The disease can affect children (1:900) and the clinical aspect is similar to that in adults, thus requiring long-term monitoring [11].

VLS has a malignant potential of around 4%, and is, therefore, considered as a means of vulvar carcinogenesis, with a recorded incidence of 32% to 76% of squamous cell carcinoma of the vulva adjacent to the lichen area [3, 7, 12, 13].

The diagnosis is clinical, but there may be uncertainty in the early stages of the disease and the main differential diagnoses are psoriasis, lichen planus, lichen simplex chronicus and benign mucous-membrane pemphigoid. A biopsy is recommended in cases that do not respond to treatment with topical corticosteroids, ulcerated lichen, or on suspicion of an invasive lesion [7, 14].

There is still no cure for VLS, so treatment is aimed at the symptoms, especially the vulvar itching, in order to prevent scarring and vulvar anatomical deformity, and to improve the quality of the sex life of patients, whom often report dyspareunia (painful intercourse), decreased orgasm and intercourse frequency compared to women who are not affected [9, 10]. Treatment is conservative using topical products [12], the gold-standard therapy is based on high-potency corticosteroid [15].

As the standard treatment can cause side effects, such as atrophy and permanent stretch marks, and still does not provide the cure, trying to find new therapies, per se*,* is an important challenging for the clinical practice. Effective alternatives that improve the excruciating skin process and optimize the quality of life in affected patients should be studied, and this is the motivation for this work, using photodynamic therapy (PDT) or photobiomodulation (PBM). There is no dosimetric protocol established for the treatment of VLS with PDT, nor with PBM. According to the literature, energy densities range from 9 to 150 J/cm^2^ and power densities from 40 to 700 mW/cm^2^ [16–21], without mentioning the studies that do not report the dosimetry used [22, 23].

There are few references in the literature about the action of PDT in vulvar lichen sclerosus [16–20, 22, 23], and till now there is no reference concerning PBM, although the anti-inflammatory and healing effects of PBM are documented in various medical and biological applications [24]. It is hoped that a prospective clinical study would contribute to more effective action in the control of this chronic skin disease, and possible understanding the mechanisms of action of these treatments.

It will be performed a comparative study among clobetasol propionate, photodynamic therapy, and photobiomodulation in patients with vulvar lichen sclerosus, using the following analyses:Clinical—by measuring the local temperature, pruritus, clamping and area of the lesion;Histological—by staining with hematoxylin & eosin;Immunohistochemical—using the markers IFN-γ, TGF-β, CD4, CD8, IL-1, p53, and Ki-67;Spectroscopic—by in vivo reflectance of skin.

## Methods/Design

The study is prospective, randomized, controlled, and conducted with 60 patients enrolled at Hospital Pérola Byington, São Paulo. The research will be undertaken in partnership with gynecologist [name], CRM 59284.

After reading, understood and signed the Free and Informed Consent, the patients will undergo a biopsy for histological confirmation of VLS, samples for laboratory tests will be collected at the beginning and end of the study: complete blood count, fasting glucose, free T4, TSH, urea, creatinine, sodium, potassium and plasma cortisol.

### Inclusion criteria

The participants in this study will be only adult female (aged over 18 years), histological diagnosed with vulvar lichen sclerosus with a normal level of cortisol, confirmed by blood test.

### Exclusion criteria

Patients with any kind of ongoing cancer and/or AIDS or coagulopathy; pregnant or breastfeeding women; patients using corticosteroids, immunosuppressants or anticoagulants; patients with renal, hepatic or pulmonary–cardiovascular failure; patients who have undergone any kind of organ transplantation in the last three years.

### Randomization and dosimetry

A researcher not involved in the study will divide the patients into three groups by randomized order (Minitab 16, EUA). Then, opaque envelopes randomly containing information about application of photobiomodulation, photodynamic therapy or corticosteroid will be labelled with sequential numbers. The researcher responsible for treatments will open the first envelope and perform the procedure written therein. The internal contents will be revealed only after statistical analysis.

The dosimetry to be used in this study is based on a pilot clinical study performed by our group, which followed the recommendations from ASLMS [21]. In brief, the aim was to compare the effects of PBM and topical corticosteroid in VLS evaluating clinical response, itching, skin thickness (atrophy), and recurrence of disease after treatments. The study was prospective, randomized, and controlled in 20 women. CAAE number of Research Ethics Committee: 34,715,314.6.3001.0069. Corticosteroid group: clobetasol propionate 0.05% ointment applied once daily at a dose of 1 g/application for 4 weeks. PBM group: methylene blue 0.01% intralesional, laser λ = 660 nm, *P* = 100 mW, *I* = 510 mW/cm^2^, E = 4 J, exposure radiant = 20 J/cm^2^, *t* = 40 s, once a week for 4 weeks. The variation in intensity of itching was compared between groups, the corticosteroid group reduced the itching at 83.75%, and the PB group decreased 50.00%. The corticosteroid group showed significant variation in the skin thickness relative to PB (*p* = 0.006). This group had a reduction in thickness of the skin −27.51%, while in PB group showed an increase of 49.07%. The treatments were completed in December 2014 and until the month of September 2015 in the corticosteroid group there was 7 patients with no symptoms, while in the PB group there was 6 patients. In the corticosteroid group, the first recurrence was two months after the treatment, while the PBM was only 4 months later.

The groups to be studied and their dosimetry are showed at Table 1.

**Table 1 Tab1:** Characteristics of the groups

Group	Number	Treatment	Parameters
GC	20	Corticosteroid over the whole vulva	Clobetasol propionate 0.05% ointment applied once daily at a dose of 1 g/application (1 g sachets) for 4 weeks
GPDT	20	Localized photodynamic therapy at 8 points of the vulva	Methylene blue 0.01% intralesional + lidocaine 2%, λ = 660 ± 10 nm, *P* = 100 mW, *I* = 510 mW/cm^2^, E = 4 J, RE = 20 J/cm^2^, *t* = 40 s, once a week for 4 weeks
GPBM	20	Localized photobiomodulation at 8 points of the vulva	The same parameters as for GPDT, except for the methylene blue, once a week for 4 weeks

Laser parameters: *λ* wavelength, *P* power, *I* irradiance, *E* energy, *RE* radiant exposure, *t* exposure time. Laser: Photon Laser III (DMC®, São Carlos/SP, Brazil). Methylene blue: Chimiolux 10 (DMC®, São Carlos/SP, Brazil). Clobetasol propionate: Drogaderma®, São Paulo/SP, Brazil)

The mode of application of photonic therapies will be by point, localized at 8 points of the vulva, as shown in Fig. 1.

**Fig. 1 Fig1:**
[figure not shown]
Photo of the vulva highlighting the 8 points of irradiation for PDT and PBM

Patients in the PDT group, upon arriving at the outpatient clinic, will be treated twice: first they will receive topical lidocaine gel 2% on the vulva and will return to the waiting room. Second: after 15 min, methylene blue with lidocaine will be injected, in a 1 to 1 ratio, at 8 points of vulva and so as to perform the PDT immediately. This procedure will be performed for the exact reason of minimizing the pain of the injection.

### Analyses

The control group (topical corticosteroid) will not be seen weekly because the standard treatment is performed by the patients themselves, in their own homes, for 30 days as recommended by the International Society for the Study of Vulvar Disease (ISSVD). In this way, all groups (GC, GPDT and GPBM) will receive treatment for 30 days and as biopsies before and after these 30 days will be compared. The study will be an open-label for patients with active symptomatic disease with a period of 12 months follow-up to determine the rate of recurrence in each arm.

#### Clinical

The temperature of the vulva will be measured with an infrared thermographic camera (C2, FLIR®, Nashua/NH, USA), which enables simultaneous measurement of the entire target area without physical contact. Measurements will be recorded as images in all sessions before, during, and after irradiation to observe the thermal fluctuation in the procedures.

In each session, the patients will be asked about the intensity of vulvar itching to assess its severity and duration, before and after irradiation, according to a visual analogical scale.

The vulvar skin clamping to evaluate the trophism will be done before irradiation at each session, using a digital caliper (Insize®, São Paulo/SP, Brazil), transversely and longitudinally in relation to the labia majora.

The area of the lesion will be monitored with a digital camera at every session (EOS Rebel T5, Canon®, Melville/NY, USA), before irradiation. To facilitate measurements, a metric scale will be placed on all vulvas for the photos. The areas of the lesions will be quantified using ImageJ software (National Institutes of Health, Maryland, USA).

The temperature, the intensity of itching, the clamping and the photographic images will be recorded for the patients of the GPDT and GPBM groups weekly for 30 days and for the GC group these measures will be done at first and 30th day.

If patients still report discomfort or undesirable symptoms from LEV after 30 days of treatment, they will continue with the same clinical protocol. If 60 days after the initiation of treatment they still remain symptomatic, the treatment that clinically appears to be better will be offered.

#### Histological

The biopsies will be performed at two points: at baseline to confirm the VLS and subsequent inclusion in the research protocol, and at the end of 30 days to investigate the prognosis after treatment. The skin fragments will be placed immediately in vials containing 4% buffered formalin, identified with the patient’s numbers and names, in accordance with the standard routine of the hospital, and sent to the Pathology Laboratory at the Hospital Pérola Byington. There will be no mention of the study group on the vials, so the analysis will be performed blind by one experienced pathologist.

Three sets of histological sections will be processed. One set will be for staining in hematoxylin and eosin in order to recognize cells and their components and to make inferences on the histology of the tissue under an ordinary optical microscope. The slides of each patient will be classified and the classifications will be assigned scores so that they can be statistically analyzed.

Another set will not be stained and will be deparaffinized for analysis of the ordering of collagen fibers under a polarized light microscope, according to an already established protocol [25]. The third and final set of histological sections will be used for the immunohistochemical technique, which is described in the next subsection. It is emphasized that the method used in the analysis of collagen ordering will be quantitative, by measuring the optical birefringence (Δn) of the samples, in nanometers.

#### Immunohistochemical

Once deparaffinized, the sections will be subjected to antigen retrieval, endogenous enzyme blocking, background blocking, incubations of antibodies, and counter-staining according to the instructions of the manufacturers of the IFN-γ, TGF-β, CD4, CD8, IL-1, p53, and Ki67 antibodies (Sigma-Aldrich®, St. Louis/MO, USA and Cell-Signaling®, Danvers/MA, USA). The cells that are positively stained by the immunohistochemical reaction will be counted by ImageJ software (National Institutes of Health, Maryland, USA) by two independent pathologists without prior knowledge of the experimental groups.

#### In-vivo reflectance spectroscopy

A portable spectrophotometer (400–900 nm) comprising a light source and a fiber-optic probe (USB2000, OceanOptics®, Dunedin/FL, USA) will be used directly on the surface of the vulvar skin in areas affected by VLS and in healthy areas of the same patients. Spectra will be taken in each session, just before the PDT and PBM. The patients in the corticosteroid group will have the spectrum recorded only twice—at baseline and after 30 days. Relative spectra will be obtained for the wavelengths corresponding to those of the therapeutic window, and the percentage of relative reflectance will be calculated.

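### No end-of-treatment reflectance spectrum is specified in the PDT and PBM arms, and no common day-30 reading is fixed for skin thickness, lesion area or itch

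*Protocol article*

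**What the plan says.** **Reflectance.** The section In-vivo reflectance spectroscopy gives one rule for the photonic arms: "Spectra will be taken in each session, just before the PDT and PBM". For controls it says: "The patients in the corticosteroid group will have the spectrum recorded only twice—at baseline and after 30 days".

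**Skin thickness and lesion area.** The Clinical section says "The vulvar skin clamping to evaluate the trophism will be done before irradiation at each session". It also says "The area of the lesion will be monitored with a digital camera at every session", and that sentence too places the photograph before irradiation. A later sentence in the same section covers temperature, itch, clamping and photographs together and has them recorded for the "GPDT and GPBM groups weekly for 30 days and for the GC group these measures will be done at first and 30th day". It does not mention spectra.

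**Itch.** In each session "the patients will be asked about the intensity of vulvar itching to assess its severity and duration, before and after irradiation". The text after Fig. 1 says of PDT patients that "first they will receive topical lidocaine gel 2% on the vulva and will return to the waiting room"; methylene blue mixed with lidocaine is injected 15 minutes later and irradiation follows at once.

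**Treatment, biopsy and analysis.** Table 1 gives both photonic treatments weekly over four weeks. The Analyses section describes a 30-day treatment period for all groups. The Histological section places the second biopsy at the end of 30 days. Statistical evaluation plans a comparison of three groups measured before and after treatment, tests clinical and spectroscopic findings between groups, and plans associations among the results.

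**The concern.** A between-arm comparison of change needs the second reading at the same time, and at the same stage of treatment, in every arm. If the last photonic reading comes before the final session while controls are read after the full course, the group-by-time contrast mixes the effect of treatment with differences in elapsed time and in treatment received. No analysis can separate these afterwards, because the missing reading was never taken.

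The planned associations suffer as well. In controls the spectrum and the second biopsy both belong to about day 30. In the photonic arms the last stated spectrum is more than a week older than the tissue it would be related to.

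**Working it through.** The 88.7% power in Statistical evaluation cannot be reproduced, because the effect size, the pilot means and SD, and the correlation between readings are not given. Nothing below depends on it. The check is of the calendar.

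**Inputs**
- Photonic sessions: weekly over four weeks (Table 1). I take this as four sessions; the count is inferred.
- Control reading: day 30 (Clinical; In-vivo reflectance spectroscopy).
- Patients: 20 + 20 in the photonic arms, 20 controls (Table 1).
- Energy: 4 J, agreeing with 100 mW × 40 s = 4 J, at 8 points (Table 1). I assume 4 J applies to each point.

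**Session days**, as start + 7 × (session number − 1):

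| Start | Sessions | Last pre-session reading | Gap to day 30 |
|---|---|---|---|
| Day 0 | 0, 7, 14, 21 | Day 21 | 30 − 21 = 9 days |
| Day 1 | 1, 8, 15, 22 | Day 22 | 30 − 22 = 8 days |

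**Treatment received before the last pre-session reading:** 3 of 4 sessions = 75%. In energy this is 3 × 8 × 4 J = 96 J of 4 × 8 × 4 J = 128 J.

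**Patients with no stated end-of-treatment spectrum:** 20 + 20 = 40 of 60.

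**Other schedule for thickness and area.** Weekly readings through 30 days fall on days 0, 7, 14, 21, 28 (or 1, 8, 15, 22, 29). The fifth follows the fourth session by 7 days and lies 2 days (or 1 day) before the control reading. The two rules thus lead to different end readings:

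| Rule in Clinical section | Last reading | Sessions completed | Gap to control reading |
|---|---|---|---|
| Before irradiation, each session | Day 21–22 | 3 of 4 | 8–9 days |
| Weekly through 30 days | Day 28–29 | 4 of 4 | 1–2 days |

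No sentence says which of these is the after value. For the spectrum only the first row is supported by the text.

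**Itch.** Each photonic session yields two scores, one before and one after irradiation. Controls have no counterpart to the second. In the PDT arm that second score follows topical and injected lidocaine. The text does not say which score enters the comparison.

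**The case against.** The strongest reply is that the weekly rule, together with the stated intention to measure every group before and after treatment, implies a reading after the fourth session. It can be added that reflectance is a side measure: the Discussion presents it as without precedent in this disease and would follow any difference with another study. A full protocol may also hold a visit schedule that an article condenses.

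Part of this stands. For thickness and area, a reader might infer that the last reading certainly precedes the fourth treatment, so that no before/after comparison exists. The documents do not support that, because the weekly rule allows a day-28 or day-29 reading. The defect there is an unresolved conflict between two rules. For the spectrum the reply fails: the weekly sentence leaves it out, and the article does give a schedule for it by arm.

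Other stronger readings also fall short.
- *Known direction of bias.* The pilot reported thickness falling by 27.51% with corticosteroid and rising by 49.07% in its photonic group, while Global benefits for the patients expects only that photonic therapy will not thin the skin. An early reading could understate thickening or understate thinning, so the sign is not fixed.
- *Damage to the power calculation.* Its inputs come from the pilot, whose listed outcomes (clinical response, itch, skin thickness, recurrence) name neither reflectance nor lesion area.
- *Itch biased towards PDT.* This would follow only if the post-irradiation score were the one compared, which is not stated.
- *A contradiction over lidocaine.* Table 1 gives PBM the PDT parameters apart from methylene blue, while lidocaine is described for PDT only. The lidocaine serves to limit injection pain and no injection is described for PBM, so this can be loose wording; a contradiction is not established.

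**Conclusion.** The point holds in a limited form. For reflectance, the plan as written confounds arm with time and treatment completed: the last stated photonic spectrum follows 3 of 4 treatments and precedes the control reading by 8 to 9 days, in 40 of 60 women. For skin thickness and lesion area, a comparable end reading is possible but not fixed. For itch, the score to be compared is not named, and one candidate is taken under local anaesthetic in one arm.

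The day counts assume four sessions exactly a week apart, starting on day 0 or day 1. That the pre-fourth-session spectrum would be set against the control day-30 spectrum is also an inference: it is the latest photonic spectrum stated, but the text does not name it as the after value. No sample-size figure changes. This is a cheap improvement to the assessment schedule and does not overturn the design.

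**What to change.** In all three arms, take the spectrum, caliper measurement, photograph, thermography and itch score at baseline and again at the day-30 biopsy visit. At both visits take them before the biopsy, with no irradiation or lidocaine beforehand. Name these two readings as the before and after values for every between-arm comparison and for associations with the biopsy. Keep the weekly and post-irradiation readings as within-arm description. Reconcile the session-tied and weekly wording in the Clinical section, and the four-week and 30-day descriptions of the treatment period.

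The cost is a few protocol sentences and one extra set of brief, non-invasive readings for 40 women at a visit they already attend for biopsy. Treatment is unchanged.

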### Global benefits for the patients

The criterion for recurrence will be pruritus, because it is the main patient complaint. The expected optical change in the skin is a reduction in reflection; lichen sclerosus leaves the skin depigmented, i.e. white, which is the color that most reflects. Therefore, as the symptoms diminish, we expect the skin to become less white, meaning that reflection also diminishes. We expect photonic therapies to decrease pruritus as much as the corticosteroid and, in addition, to not decrease the thickness of the skin, avoiding stenosis and pain.

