On the other hand, methylene blue (MB) acting as the photosensitizer makes PDT more reasonable in clinical practice, especially in the Public Health System, since it has a high quantum yield of singlet oxygen and the ability to generate several radical species, it is highly photostable, easily eliminated from the body, presents minimal toxicity and low cost [33]. Moreover, the MB has an affinity for melanin, it is more lipophilic than ALA, actively binds to mitochondria and provides a mechanism for the reduction of the inflammatory response [34, 35]. The monomers and dimers of MB have distinct absorption spectra: the monomers have maximum absorption at 664 nm and the dimers at 590 nm. It is known that in a 20 μM aqueous solution there are only monomers present. A detailed review of the characteristics of MB can be found in the study of Tardivo et al. [36].

In PBM, the power density is not sufficient to induce biological activity dependent on the temperature increase, provided that the recommendations of the World Association for Laser Therapy (WALT) are followed [31]. It can be used with radiation sources that are coherent (lasers) or incoherent (lamps and LEDs). The basic biological mechanism that is currently accepted for explaining, although not completely, the effects observed in PBM is the absorption of red and infrared radiation by chromophores in mitochondria, in particular cytochrome c oxidase, and photoreceptors in the plasma membrane of cells, respectively [30]. The main reported effects are the reduction of pain and inflammation, optimization of tissue repair, tissue and nerve regeneration, and the repigmentation of skin lesions [24]. While these effects are desirable in the treatment of VLS, to date no work has been found associating it with PBM.

Nowadays we know that immunohistochemistry is an indispensable technique for solving differential diagnosis problems caused by basic routine staining of HE [32]. Although we know that the diagnosis of LEV is clinical, we insist to collect the biopsies so that we can cross-check the data (HE versus immunohistochemistry) for a better understanding of the disease and the mechanisms involved after the different therapies. We remember that VLS has a malignant potential of around 4%, and is, therefore, considered as a means of vulvar carcinogenesis, with a recorded incidence of 32% to 76% of squamous cell carcinoma of the vulva adjacent to the lichen area.

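### Methylene blue is injected in the PDT arm only and absorbs in the measured reflectance range, and the plan has no way to tell residual dye from recovery

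*Protocol article*

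**What the plan says.** Five statements in the protocol article bear on this point.

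- **What is measured.** In-vivo reflectance spectroscopy: "A portable spectrophotometer (400–900 nm) comprising a light source and a fiber-optic probe". The analysed part is described as follows: "Relative spectra will be obtained for the wavelengths corresponding to those of the therapeutic window". No limits in nanometres are given for that window.
- **When.** The same section: "Spectra will be taken in each session, just before the PDT and PBM". The corticosteroid arm is measured at baseline and after 30 days only.
- **Who receives dye.** Table 1 gives the PDT arm "Methylene blue 0.01% intralesional + lidocaine 2%, λ = 660 ± 10 nm", weekly for four weeks, and the PBM arm "The same parameters as for GPDT, except for the methylene blue, once a week for 4 weeks". The corticosteroid arm receives ointment only. The text after Fig. 1 adds that "methylene blue with lidocaine will be injected, in a 1 to 1 ratio, at 8 points of vulva", with the light given straight afterwards.
- **Where the dye absorbs.** Discussion: "the monomers have maximum absorption at 664 nm and the dimers at 590 nm".
- **How the result is read.** Global benefits for the patients: "The expected optical change in the skin is a reduction in reflection", because the skin is expected to become less white as symptoms ease. Statistical evaluation submits the spectroscopic findings to tests between the treatment groups and examines their associations with the other results.

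**The concern.** An absorbing dye in the skin lowers reflectance, and the plan takes lower reflectance as a sign of recovery. Dye and arm are completely confounded, so any dye present at a measurement cannot be separated from a PDT effect. The article describes no wash-out, no check for residual dye and no analysis that leaves out the dye's absorption band.

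At stake are the between-arm test of reflectance and the planned associations of reflectance with the clinical, histological and immunohistochemical results. The end of the Discussion also makes a further, more detailed optical study depend on finding significant spectral differences, so an artefact could prompt that study.

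**Working it through.** There is no stated figure to reproduce. The check sets the statements side by side and then asks how the answer depends on what is not stated.

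**1. Is the dye inside the analysed band?** Both peaks (590 and 664 nm) lie within 400–900 nm. The window has no stated limits, but the laser is at 660 ± 10 nm and the Discussion says that photosensitizer and light source must match optically. The 664 nm peak is therefore very probably inside it. The 590 nm peak may not be, and the point does not need it.

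**2. Does a healthy-skin reference remove it?** Spectra are taken in affected and healthy areas of the same patient, but the article does not define what the relative reflectance is relative to. If the reference is healthy skin without dye, dye in the lesion does not cancel.

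**3. Which way does dye push the change from baseline?** Assumptions: sessions on days 1, 8, 15 and 22; equal doses; first-order loss with half-life h days; log reflectance falling in proportion to dye present. The article does not say whether the last spectrum in the PDT arm is at session 4 or at day 30, so both are shown.

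Let r = 2^(−7/h). Residue, as a share of one dose:

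- before session 2: r
- before session 3: (r + 1)r
- before session 4: R4 = [(r + 1)r + 1]r
- at day 30: R30 = (R4 + 1) × 2^(−8/h)

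Example, h = 3: r = 0.198; before session 3, 1.198 × 0.198 = 0.238; R4 = 1.238 × 0.198 = 0.246; R30 = 1.246 × 0.157 = 0.196.

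Dye at the last reading minus dye at baseline:

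- Spectra before injection (baseline dye 0): R4 at session 4, R30 at day 30.
- Spectra after injection (baseline dye 1): (R4 + 1) − 1 = R4 at session 4, R30 − 1 at day 30.

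A positive value favours PDT and a negative value works against it.

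| Assumed half-life (days) | Session 4, either order | Day 30, spectra before injection | Day 30, baseline spectrum after injection |
|---|---|---|---|
| 0.5 | +0.01% | 0.0% | −100.0% |
| 1 | +0.8% | +0.4% | −99.6% |
| 3 | +24.6% | +19.6% | −80.4% |
| 7 | +87.5% | +84.9% | −15.1% |
| 14 | +156.1% | +172.3% | +72.3% |

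With spectra before injection, the distortion can only favour PDT, and it ranges from nothing to large. With spectra after injection and a day-30 final reading, it mostly runs against PDT.

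**4. How sensitive is the outcome?** These are free assumptions, not estimates for this trial. An added absorbance A lowers reflectance at that wavelength by 1 − 10^(−A): 2.3%, 10.9%, 20.6% and 36.9% for A = 0.01, 0.05, 0.10 and 0.20. This is the effect at the dye wavelength, not across the window. For a two-arm comparison with 20 per arm and no true difference, a shift of b standard deviations gives a rejection probability of Φ(b/√(2/20) − 1.96) + Φ(−b/√(2/20) − 1.96). That is 6.2%, 12.4% and 35.3% for b = 0.10, 0.25 and 0.50, against a nominal 5%.

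**The case against.** The strongest reply is that dye in the skin at measurement is never shown. The Discussion defines PDT as photosensitizer plus light, so a spectrum taken before the PDT naturally precedes both. The light follows the injection at once, which leaves little room for spectra in between. Any effect then rests on residue at least a week old, and the only remark on clearance is that the body removes the dye readily. The article also does not say that the probe sits on the injected points. Reflectance is presented as exploratory, and the order of steps within a visit is a detail that a condensed article may leave to the full protocol.

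Most of this stands. The pre-injection reading is the more natural one, and a reader who inferred that the comparison is biased toward PDT would go beyond the text: presence of dye is unproven, and in one ordering the distortion partly cancels or reverses. A reader might also infer that staining shrinks the lesion area traced on photographs. The article does not say that lesions are traced by whiteness, nor that staining is visible, so this is not supported.

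What the reply does not remove is the structure. General clearance from the body is not clearance from an intralesional injection, and the same paragraph of the Discussion calls the dye highly photostable and says it binds melanin and mitochondria. Settling the order of steps would still leave carry-over indistinguishable from recovery.

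**Conclusion.** The point holds as an uncontrolled possible bias, not as a demonstrated one. The article establishes that the dye is given in one arm only, that it absorbs within the recorded and very probably the analysed range, that lower reflectance is read as improvement, and that the arms are compared on it.

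The size and, if spectra follow the injection, the direction are open: they depend on the order of steps, the time of the last reading and a skin clearance rate that is not given. The figures above show this dependence and are not evidence that bias will occur. With spectra before injection and a half-life of a day or less, the problem is negligible (under 1% of a dose).

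Pruritus, and recurrence judged by it, are not affected. The matter is worth correcting because, as written, a reflectance difference for PDT could not be interpreted.

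**What to change.** 1. State that every spectrum, including baseline and day 30, is taken before any injection on that day.
2. Keep the planned therapeutic-window analysis. Add a pre-specified between-arm analysis that leaves out the dye absorption band in all arms (around 590–664 nm, limits set from the dye's own spectrum) and retains the unaffected visible wavelengths where possible. Moving the main comparison to the near infrared would not be a good substitute, because the stated hypothesis is about whiteness, which is a property of visible light.
3. Report the dye band separately, PDT arm against PBM arm, as a check for residual dye.
4. State that a reflectance difference in the PDT arm will be attributed to recovery only if it persists outside the dye band.

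The cost is a sentence on measurement order and a little more analysis of spectra already planned. The downside is a narrower band in the added comparison. No treatment changes.
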